### Plans to give access to the full protocol, participant-level data, and statistical code {31c}

Access to the full protocol and participant-level data will be given on request from the corresponding author.

#### Composition of the data monitoring committee, its role and reporting structure {21a}

##### Data monitoring

In light of the short duration of the study and minimal risk to participating neonates, we have decided not to form a formal data monitoring committee (DMC).

#### Adverse event reporting and harms {22}

##### Harms

We will define an adverse event as any untoward medical occurrence in a subject without regard to the possibility of a causal relationship. Adverse events will be collected after the subject has provided consent and enrolled in the study. All adverse events occurring after entry into the study and until hospital discharge will be recorded. An adverse event that meets the criteria for a serious adverse event (SAE) between study enrolment and hospital discharge will be reported to the local Ethical Committee. A serious adverse event for this study is any untoward medical occurrence that is believed by the investigators to be causally related to study intervention and results in any of the following: life-threatening condition (that is, immediate risk of death), severe or permanent disability, and prolonged hospitalization. Serious adverse events occurring after a subject is discontinued from the study will *not* be reported unless the investigators feel that the event may have been caused by the study drug or a protocol procedure. The following AE will be reported: feeding intolerance defined as vomiting and emesis, abdominal distention, and gastric residuals within 7 days after the introduction of TEN. SAE will include necrotizing enterocolitis and gastrointestinal obstruction occurring after the introduction of TEN. Adverse events will be collected within the e-CRF and reported in trial publications.

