#### Secondary outcomes

Growth (weight, length, head circumference) will be assessed at discharge and at 4 months of corrected age.Body composition (percentage of body fat, fat mass, fat-free mass) will be measured at discharge and at 4 months corrected age by air plethysmography (PeaPod).^1^Neurodevelopmental outcome:
12 months corrected age: BSID-III (Bayley Scale of Development Third Edition); the following stratification of index composite scores will be used in our study:< 70 (> 2 SD below the mean)—severe impairment70–84 (> 1 SD below the mean)—mild impairment≥ 85—normal development3.5 years of corrected age: BSID and WPSSI-IV (Wechsler Preschool and Primary Scale of Intelligence, Fourth Edition IV).Behavioural problems: parental assessment by CBCL (Child Behaviour Check List) at 3.5 years corrected age.Feeding tolerance under whole period of fortification.Morbidity: incidence of necrotizing enterocolitis (NEC), retinopathy of prematurity (ROP) and bronchopulmonary dysplasia (BPD), intraventricular haemorrhage (IVH), periventricular leukomalacia (PVL), sepsis, and pneumonia. Definitions provided below.

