##### Definitions

Feeding tolerance: defined as haemorrhagic residuals or vomiting bile until pathological causes are ruled out (intestinal obstruction or ileus) [17]. Gastric residuals and abdominal girth will not be checked routinely. Isolated green or yellow residuals will be considered unimportant.NEC (necrotizing enterocolitis): stage II or III. Stage II requires clinical manifestations of distended abdomen and radiological verification (intramural and/or portal gas). Stage III requires findings like in stage II and more severe clinical symptoms (shock, need for respirator). In surgery verified cases, no radiological verification is needed [18].ROP (retinopathy of prematurity): stages I to V, diagnosed by an ophthalmologist according to international criteria [19].BPD (bronchopulmonary dysplasia): need for oxygen, continuous positive airway pressure (CPAP), or mechanical ventilation at 36 + 0 weeks gestational age [20].IVH (intraventricular haemorrhage) [21].PVL [21].Early- and late-onset sepsis defined as a positive blood or cerebral fluid culture at less or more than 72 h of age, respectively [22].

Feeding tolerance has been chosen as an efficacy and harm outcome in order to evaluate whether TEN may impact milk absorption in the intervention group. Exclusive breastfeeding decreases the risk of NEC; however, the impact of TEN on the risk of developing NEC has not yet been studied. Blood culture confirmed early-onset sepsis (EOS) is a known risk factor for delayed implementation of EN and can impact the risk of late-onset sepsis (LOS). Diagnosis of EOS and LOS can be associated with intermitted withdrawal of enteral nutrition, BPD, IVH, and PVL which are markers of neonatal morbidity; hence, we decided to include them in our analysis.

Time schedule of enrolment, interventions (including any run-ins and washouts), assessments, and visits for participants is presented in Table 2.

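### The harms rules build causality into the SAE definition, leave out death, and time the named events from a feeding regimen that only one arm receives, so SAE reports and those counts have no like-for-like control window

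*Protocol article*

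**What the plan says.** All of the following is in the protocol article.

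- **Adverse events (Harms).** An adverse event is "any untoward medical occurrence in a subject without regard to the possibility of a causal relationship". The recording rule is broad: "All adverse events occurring after entry into the study and until hospital discharge will be recorded".
- **Serious adverse events (Harms).** An SAE is "any untoward medical occurrence that is believed by the investigators to be causally related to study intervention and results in any of the following": an immediate threat to life, severe or lasting disability, or a longer hospital stay. An event meeting the SAE criteria "between study enrolment and hospital discharge will be reported to the local Ethical Committee".
- **Named events (Harms).** The named adverse event is feeding intolerance, made up of vomiting, abdominal distension and "gastric residuals within 7 days after the introduction of TEN". The named SAEs are NEC and gastrointestinal obstruction, also counted once TEN has been introduced.
- **Outcomes (Secondary outcomes).** Morbidity covers NEC, ROP, BPD, IVH, PVL, sepsis and pneumonia. Tolerance is listed as "Feeding tolerance under whole period of fortification".
- **Definitions.** Feeding tolerance is defined through haemorrhagic residuals or bile vomiting, and "Gastric residuals and abdominal girth will not be checked routinely".
- **Oversight (Data monitoring; Interim analyses).** There is no data monitoring committee and no interim analysis. The reasons given are the short duration and low risk.

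**The concern.** Three features of the SAE rules pull in the same direction.

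1. Seriousness and causality are normally judged separately. Here an event that is plainly serious but thought unrelated is not an SAE at all. In very preterm infants most serious events have several plausible causes, so the belief that one is unrelated is easy to reach and hard to test. A real excess in one arm may become visible only by counting events regardless of attribution.
2. Death is missing from the seriousness criteria and is not named as an outcome.
3. The events most relevant to the intervention are dated from an exposure that one arm never has. A count with a defined start in one arm and none in the other cannot be read as a comparison.

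With no monitoring committee and no interim look, SAE reporting to the ethics committee is the main route described by which accumulating harm would reach an independent body. The Definitions section itself says that the effect of TEN on NEC risk has not been studied, so this route should not depend on investigators' attribution.

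**Working it through.** The plan gives no figure on this point and none can be recomputed, so the check sets the texts side by side.

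**Step 1: what TEN means.** TEN is not in the abbreviation list. The title of Fig. 1 refers to tailored enteral nutrition. The Definitions section speaks of the effect of TEN on milk absorption in the intervention group. The Intervention description says that milk is analysed in both arms but only the intervention group receives targeted fortification. On these texts, introduction of TEN is a date that exists only in the targeted arm.

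**Step 2: where death appears.** It is not in the Secondary objectives, in the Secondary outcomes, in the list repeated under Plans for assessment and collection of outcomes, or among the three SAE consequences. As a trial event it appears only among the Exclusion criteria.

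**Step 3: apply the rules, read literally, to an event before discharge.**

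| Event | Targeted arm, after TEN starts | Standard arm | Also a listed outcome in both arms? |
|---|---|---|---|
| NEC | Named SAE; that sentence sets no causality condition | SAE only if believed causal and with one of the three consequences; otherwise AE | Yes |
| Gastrointestinal obstruction | Named SAE, as above | As above | No |
| Vomiting, distension or residuals within 7 days | Named AE | Window has no start; general AE only | Feeding tolerance is, but with other signs and another window |
| Sepsis judged unrelated | AE only | AE only | Yes |
| Death judged unrelated | AE only | AE only | No |

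The first three rows show the missing control window. The last row is the same in both arms: such a death generates no SAE report. If the infant also had NEC or obstruction after TEN began, that event would be reported as a named SAE, but the death itself would still not be a criterion. A death believed causal would presumably enter as life-threatening.

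**Step 4: the feeding-intolerance texts.**

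| Section | Signs | Period |
|---|---|---|
| Harms | Vomiting, abdominal distension, gastric residuals | 7 days from TEN |
| Definitions | Haemorrhagic residuals or bile vomiting; residuals and girth not routinely checked | Not stated |
| Secondary outcomes | Not stated | Whole fortification period |
| Criteria for discontinuing | Distension increase above 2 cm and/or regurgitation after more than 3 feeds a day | Not stated |

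The Harms definition counts two signs that the Definitions section says will not be looked for routinely, and the two windows differ. These passages, and the discontinuation criterion that relies on a measured change in distension, must be reconciled.

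**The case against.** The strongest reply is that the protocol has other ways of capturing harm. Adverse events of any cause are recorded from study entry to discharge with no arm condition, and the Harms section says they will appear in trial publications. NEC, sepsis and five other morbidities are outcomes without any causality or TEN condition. Comparing NEC, ROP and BPD between groups is a stated objective, and the Statistical methods give secondary and safety outcomes a two-sided test. Treating physicians and bedside nurses are said to be blinded, which limits attribution that differs by arm. Osmolality checks, weekly BUN and audit of adverse event records also continue throughout.

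Most of this stands, and it rules out three stronger readings.

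- A reader might infer that harms cannot be compared between arms at all. The general recording rule and the both-arm morbidity outcomes contradict that.
- A reader might infer from the Exclusion criteria, which list NEC, sepsis and death without a time point, that infants with these events after randomisation would be removed. The sections on implementation, retention and missing data keep discontinued infants on study and in the intention-to-treat analysis, so the list is awkwardly worded but does not delete events.
- A reader might infer that the 7-day window covers only about 4 days at full fortification (7 minus the 3-day step-up). This assumes that TEN is introduced on step-up day 1. The Intervention description marks day 4 as the start of the intervention period, and on that reading all 7 days are at the full amount. The protocol does not say which applies.

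The reply does not cover obstruction or death, which are not listed outcomes. It does not repair the SAE channel, since general adverse events are not what goes to the ethics committee. Blinding is only partial reassurance: the Intervention description has attending physicians approving the targeted prescriptions and bedside nurses preparing the milk with the additives. Staff who truly are blinded could not apply a rule dated from TEN without knowing the arm.

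**Conclusion.** The concern holds for SAE reporting, for the counts anchored to TEN, and for mortality. As written, those counts have no like-for-like control window. A death thought unrelated is a generic adverse event that does not reach the ethics committee, and all-cause death is not an outcome.

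The size is qualitative: no event rate, power or sample size is involved. The growth outcome and the comparisons of NEC, sepsis and other listed morbidity are unaffected. The conclusion rests on a literal reading of the Harms section and on TEN meaning tailored enteral nutrition. If TEN were meant to cover fortification in both arms, the timing problem would go, but the causality condition and the omission of death would remain. The conflict over feeding intolerance does not depend on either assumption.

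**What to change.** Amend the Harms and Outcomes sections as follows.

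1. Define seriousness by consequence alone, with death included, and record the investigator's view of causality in a separate field.
2. Add all-cause death as a safety outcome.
3. Count the named adverse event and the named SAEs from randomisation to discharge in both arms, and spell out TEN wherever it is kept.
4. Adopt one feeding-intolerance definition and one window for outcome and harm reporting, using signs recorded in the same way in both arms. Reconcile the Harms, Definitions, Secondary outcomes and discontinuation passages with one another. Which signs to use is for the clinical team.

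This needs a protocol amendment and e-CRF changes, with no extra infants or visits. The downside is more SAE forms, many for events expected in this population.

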The desired macronutrient concentration in breast milk will be 4.4 g/100 ml of fat, 3 g/100 ml of protein, and 8.8 g/100 ml of carbohydrate in order to meet the European Society for Paediatric Gastroenterology, Hepatology, and Nutrition (ESPGHAN) guidelines (6.6 g/kg/day of fat, 4.5 g/kg/day of protein, and 13.2 g/kg/day of carbohydrate) assuming an intake of 150 ml/kg/day.

Target fortification (TF) will be done in 3 steps:
Determination of macronutrient concentration in own OMM/HDMSF: human milk fortifier, HMF NutriciaTF: adding fat, protein, and/or carbohydrate to achieve target levels of macronutrients

In cases where a macronutrient component after SF will exceed the target value, only the other deficient macronutrient components will be adjusted.

To enhance feeding tolerance at the start of the intervention, TF will be gradually introduced in a stepwise manner over a 3-day period (maximum target dosage of added fat, protein, and carbohydrate will be as follows: at day 1, 0.3 g; day 2, 0.6 g; and day 3, 0.9 g per 100 ml breast milk), as suggested by Rochow et al. [12]. On day 4, the full amount of target fortification for each macronutrient will be prescribed; this day will be marked the starting point of the intervention period. Patients will be fed every 3 h via a gastric tube by registered nurses. Starting from 33 weeks of post-conceptional age (PCA), non-nutritive sucking stimulation will be initiated by occupational therapists. At approximately 34 weeks of PCA, infants will be transitioned to bottle feeding. When breastfeeding is established, patients will receive TF as one or two bottle feeds.

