As a safety assessment to ensure that an appropriate amount of fortifier is added, osmolality of unfortified and FBM samples will be measured 3320 with the use of Micro-Osmometer; Advance Instruments, Norwood, MA. Bedside nurses will be then informed whether the osmolality of FBM is within the acceptable target range (400–480 mOsmol/kg) before the milk administered during the next 12-h shift. Osmolality lower or higher than the defined target range will be considered as a sample preparation error of fortification, and a new batch of breast milk will be prepared. Prescription of TF will be completed before noon. The attending physician will then approve these prescriptions. Subsequently, individual additives will be provided by nutrition services. Bedside nurses will prepare batches of FBM including the additives for target fortification and divide it into single feeding portions to be given to infants. Blood urea nitrogen will be used as a surrogate for protein nutriture and will be monitored weekly [16].

The intervention will continue until 37 weeks of post-conception age or hospital discharge. Parents, attending physicians, and outcome assessors will be blinded to the intervention.

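### The feeding-intolerance adverse event is defined only for the first 7 days after TEN is introduced, so later non-bilious vomiting or distension falls in no defined feeding-tolerance measure

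*Protocol article*

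**What the plan says.** Adverse event reporting and harms {22} lists, as the adverse event to be reported, "feeding intolerance defined as vomiting and emesis, abdominal distention, and gastric residuals within 7 days after the introduction of TEN". NEC and gastrointestinal obstruction are named in the same section as serious events, with no 7-day limit. That section also has a general rule: "All adverse events occurring after entry into the study and until hospital discharge will be recorded". It adds that adverse events go into the e-CRF and into the trial publications.

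On dosing, Intervention description {11a} states that "TF will be gradually introduced in a stepwise manner over a 3-day period". The full amount is prescribed on day 4, which the protocol marks as the start of the intervention period. "The intervention will continue until 37 weeks of post-conception age or hospital discharge".

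The list of secondary outcomes under Outcomes {12} includes "Feeding tolerance under whole period of fortification". The Definitions that follow describe feeding tolerance as "defined as haemorrhagic residuals or vomiting bile until pathological causes are ruled out" and add that "Gastric residuals and abdominal girth will not be checked routinely". They also say that the outcome was "chosen as an efficacy and harm outcome in order to evaluate whether TEN may impact milk absorption in the intervention group".

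Criteria for discontinuing {11b} makes increasing distension of more than 2 cm, or regurgitation after more than 3 feeds a day, a reason to stop the allocated intervention, with no time limit. Statistical methods {20a} says that secondary and safety outcomes will be tested two-sided for superiority, without listing the safety outcomes.

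**The concern.** The protocol has two feeding-tolerance measures, and neither covers the ordinary signs of intolerance over the whole treatment period. The adverse event has the broad definition (any vomiting, distension, residuals) but a short window. The secondary outcome has the long window but a narrow definition. Non-bilious vomiting, or distension that is not part of stage II or III NEC, falls between them once the first week has passed.

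This matters because the protocol treats feeding tolerance as a harm outcome, and poor tolerance is a plausible harm of adding fat, protein and carbohydrate to milk. Exposure also keeps changing after the first week: additives are recalculated from milk analyses three times a week, and infants move to bottle feeding at about 34 weeks. The discontinuation rule shows that distension and regurgitation are taken seriously throughout.

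A second weakness concerns the starting point. The window opens at the introduction of TEN, which the Definitions tie to the intervention group. No equivalent day is stated for the standard arm, so it is unclear which 7 days would be counted there.

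**Working it through.** The plan gives no figure for this point, so there is none to reproduce. The check has two parts.

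**1. Which signs are covered, and when**

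| Sign | First 7 days after TEN | Later, to end of fortification |
|---|---|---|
| Haemorrhagic residuals, bilious vomiting | Adverse event and secondary outcome | Secondary outcome |
| Non-bilious vomiting | Adverse event | General adverse-event recording only |
| Distension without NEC | Adverse event | General recording; stopping rule if more than 2 cm |
| NEC, gastrointestinal obstruction | Serious adverse event (NEC also an outcome) | Serious adverse event (NEC also an outcome) |

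The gap is the last column of the second and third rows.

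**2. How much exposure the window holds**

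Inputs from the protocol: a 3-day step-up with full dose from day 4; a 7-day window; an end at 37 weeks or discharge; gestational age at birth up to 32 weeks. The eligibility section says full enteral feeding is usually reached at 7 days of life at the earliest. The protocol gives neither actual start days nor discharge dates, so I assume a start on day 10 of life for births at 24–30 weeks and day 7 for births at 32 weeks.

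With G the gestational age at birth, E the end week and s the start day:

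- total fortified days T = 7 × (E − G) − s
- full-dose days F = T − 3
- window counted from step-up day 1: 3 step-up days + 4 full-dose days, share = 4/F
- window counted from day 4: 7 full-dose days, share = 7/F

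Treatment to 37 weeks:

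| G | s | T | F | 4/F | 7/F |
|---|---|---|---|---|---|
| 24 | 10 | 81 | 78 | 5% | 9% |
| 26 | 10 | 67 | 64 | 6% | 11% |
| 28 | 10 | 53 | 50 | 8% | 14% |
| 30 | 10 | 39 | 36 | 11% | 19% |
| 32 | 7 | 28 | 25 | 16% | 28% |

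The share rises when full dosing ends sooner:

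- G = 28, s = 10, full dosing only to 34 weeks (an assumption, because infants move to bottle feeding about then and, once breastfed, receive targeted fortification in only one or two bottle feeds): F = 7 × 6 − 10 − 3 = 29; 4/29 = 14%, 7/29 = 24%.
- G = 28, discharge at 35 weeks, s = 7 or 10: F = 39 or 36; 4/F = 10% or 11%.
- G = 32, discharge at 35 weeks, s = 7 or 10: F = 11 or 8; 4/F = 36% or 50%.
- G = 32, discharge at 34 weeks, s = 7: T = 7, F = 4; the window covers all full-dose exposure, 100%.

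**The case against.** The strongest reply is that the protocol says this event will be reported; it does not say that a comparison between arms ends on day 7. All adverse events are recorded to discharge and are to be published, and safety outcomes are to be tested two-sided with no 7-day restriction. A reader might infer that later intolerance is lost, or barred from comparison. The documents do not support that. What stands is narrower: later non-bilious events have no definition as a feeding-tolerance measure, so whether and how they are tabulated is left open.

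Second, an early window may be deliberate. The step-up is there to help tolerance at the start, so early mild signs are a sensible focus, while NEC, obstruction and the stopping rule pick up serious later cases. This justifies keeping an early window, but not making it the only one. Discontinuation for intolerance is also not listed as an outcome.

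Third, table layout belongs in an analysis plan, which is not shown. That is true of layout in general, but here the protocol itself fixes a restrictive definition.

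Fourth, the share depends on the anchor and on how long full dosing lasts. This is right. Because the protocol marks day 4 as the start of the intervention period, both anchors are shown, along with shorter dosing.

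**Conclusion.** The point holds as a minor weakness in how a harm is defined. The only named non-serious adverse event stops after one week, and the whole-period outcome is too narrow to take over from it. The start of the window is also undefined in the standard arm.

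Under the assumed start days and treatment to 37 weeks, the window holds 5–16% of full-dose days from step-up day 1, or 9–28% from day 4. It holds more with earlier discharge or reduced dosing after about 34 weeks, and everything for a birth at 32 weeks discharged at 34. It would be tempting to read the remainder as the proportion of intolerance events missed. The documents do not allow that: they give no timing of events, and intolerance may well cluster early. No recorded data are lost, and the primary analysis and sample size are unaffected.

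**What to change.** In Adverse event reporting and harms {22}, replace the 7-day limit with a period that runs from the first study-fortified feed after randomization to the end of the intervention (37 weeks or discharge). This start exists in both arms. Report by arm the number and proportion of infants with at least one event, and keep the first 7 days from the same start as a separate row. Also report by arm the number of infants discontinued for poor feeding tolerance under {11b}.

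The cost is a reworded sentence and a longer adverse-event table. No new data collection is needed, since adverse events are already recorded to discharge. The reported rate will be higher than with the 7-day window. Because residuals and girth are not checked routinely, those components will reflect only what staff happen to notice, so vomiting will be the most reliable one; the report should say so.
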